## Abstract

**Background:** Gestational diabetes (GDM) is associated with adverse short- and long-term maternal and fetal outcomes. Observational data support a link between sleep-disordered breathing (SDB) during pregnancy and GDM. However, it is unknown whether treatment of SDB with continuous positive airway pressure (CPAP) improves glucose control in this patient population. In addition, CPAP adherence and feasibility as a treatment option in pregnancy is unknown. This pilot randomized, controlled trial aims to primarily determine the feasibility of CPAP treatment in pregnant women with SDB and GDM. This study is also investigating the effect of SDB treatment on 24-h glucose profiles as an exploratory outcome.

**Objectives:** To describe the study methodology in this ongoing study of pregnant women with GDM and SDB.

**Patients and Methods:** Pregnant women with GDM and SDB defined by apnea-hypopnea index (AHI) ≥10 (Chicago Scoring Criteria) on level 2 polysomnography are randomized to either auto titrating CPAP (experimental group) or a nasal dilator strip (control group) until delivery. The primary outcome, objectively-assessed adherence to CPAP, is measured over the course of the treatment period using device-specific software. Recruitment and retention rates will be calculated to assess the feasibility for planning future trials. Twenty-four hour glucose profiles are measured over a 72-h period using the continuous glucose monitoring (CGM) system, before and after the intervention.

**Conclusion:** The results of this study will be highly informative to determine whether CPAP is a feasible treatment for pregnant women with GDM and SDB, a specialized population at risk for substantial comorbidity. The trial results will ultimately be useful in planning future SDB treatment trials in pregnancy and GDM.

The study is registered on clinicaltrials.gov (NCT02245659).

## Introduction

Gestational diabetes (GDM) is glucose intolerance that is first recognized during pregnancy (1). The prevalence of GDM doubled between 1994 and 2002 in a multi-ethnic U.S. population (2), possibly related to the global epidemic of obesity. Current estimates of prevalence range from 8 to 16%, depending on the study population and diagnostic criteria used (3, 4). Maternal hyperglycemia can lead to both short-term and long-term adverse outcomes for both the mother and baby, including increased rates of preeclampsia, perinatal mortality, cesarean section, neonatal metabolic abnormalities, macrosomia and resulting birth injuries (5). In addition, in the long-term, a history of GDM in women is associated with an increased risk of developing cardiovascular disease (6–8), type 2 diabetes (9, 10) and non-alcoholic fatty liver disease (NAFLD) (11, 12). Although the majority of GDM cases arise during pregnancy and resolve after delivery, long-term follow-up studies demonstrate that ~20–50% of women progress to type 2 diabetes, a risk which has doubled over the past 10 years (13–16). Moreover, there is also an increased risk for developing metabolic syndrome and being overweight later in life among offspring exposed to GDM (17–20). Thus, prevention and improved management of GDM may improve outcomes for both the mother and offspring.

Sleep-disordered breathing (SDB) is prevalent in 17–45% of pregnant women by the third trimester (21–25), depending on the diagnostic cut-offs used, degree of obesity, and comorbidities present in the study population. SDB is characterized by breathing pauses during sleep, which results in sleep disruption from frequent arousals and intermittent hypoxia. Similar to polysomnography-based estimates of SDB prevalence, symptoms of SDB are reported in 14–35% of pregnant women by the 3rd trimester (26–28). In addition to weight gain, pregnancy-specific physiological changes that include upper airway narrowing, vascular congestion, nasal congestion and decreased functional residual capacity (29, 30) are hypothesized to increase the risk of SDB. In several studies that have adjusted for obesity, SDB in the non-pregnant population is associated with glucose intolerance and type 2 diabetes (31, 32). Although the specific mechanisms of this relationship have yet to be clearly defined, pathways involving increases in sympathetic drive, cortisol, and inflammation, are likely involved (33, 34). Extrapolating from the non-pregnant literature, SDB may also represent a novel risk factor for GDM (21, 31, 35). Two recent meta-analyses of observational studies demonstrated an increased risk of GDM in maternal SDB (36, 37) (adjusted odds ratios of 1.86–3.06). More recently, publication of the nuMoM2b cohort sleep substudy, which assessed SDB in pregnancy in the largest cohort to date (*n* = 3,705), revealed similar results between the presence of SDB in pregnancy and the risk of GDM (odds ratios ~3) (38).

Despite the accumulating evidence that gestational SDB is associated with GDM, the data are limited by the biases inherent in observational studies, particularly with possible residual confounding from obesity. Performing controlled interventional studies with treatment of SDB is the next essential step to determine whether there is an associated improvement in outcomes. Our ultimate objective is to perform a large-scale, multi-center randomized trial evaulating the effects of CPAP treatment of SDB on glycemic control in GDM. To date, a few studies, mostly uncontrolled and all with small sample sizes, have investigated whether treatment of SDB with CPAP improves blood pressure among patients with gestational hypertension or preeclampsia [Reviewed in (21)]. In a recently published trial of CPAP vs. no CPAP for 2 weeks in women with GDM, of the 15 women on CPAP, only 7 were adherent (minimum usage 4h/night for > 70% of nights) (39). However, adherence to CPAP for a longer duration during pregnancy and its effect on 24-h glucose profiles is unknown.

Several CPAP trials in non-pregnancy that have failed to demonstrate improvements with respect to metabolic outcomes have also been limited by poor CPAP adherence [reviewed in (31)]. Optimizing CPAP use, on the other hand, has improved cardiometabolic outcomes (40–45), particularly in in-laboratory proof-of-concept studies with 8 h a night of CPAP use in patients with prediabetes (46) and type 2 diabetes (47). In pregnancy, CPAP adherence may be further affected by the unique sleep complaints that are prevalent in pregnancy, including less deep sleep and more frequent nocturnal awakenings (48). In order to appropriately power large, multi-center trials in pregnant women with SDB for improving cardiometabolic outcomes, the adherence to CPAP among pregnant women needs to first be established. As such, the primary aim of this pilot trial is to assess the adherence to CPAP in pregnant women with GDM, a unique population at risk for significant comorbidity. The secondary aims are to collect pilot data on glycemic control in the form of 24-h continuous glucose monitoring (CGM) as well as other relevant outcomes to allow planning and sample size calculations for a future, multi-center trial with the primary aim of evaluating the effects of SDB treatment on glycemic control in GDM.

## Methods

### Trial protocol

This is an unblinded, randomized-controlled parallel study. Figure 1 demonstrates the protocol design and testing at each visit. Recruitment started in March 2015 at two centers in Montreal, Canada (McGill University Health Centre and Centre Hospitalier Universitaire Sainte-Justine).

**Figure 1 F1:**
[figure not shown]
The trial protocol involves a baseline evaluation that initially confirms the diagnosis of gestational diabetes (GDM). This testing usually takes place between 24 and 28 weeks of gestational age. During the baseline visit, participants wear an Armband, consisting of an accelerometer, for 1 week in order monitor activity levels and sleep-wake patterns. Insertion of a continuous glucose monitoring (CGM) device for 72 h takes place at this visit. Within 1–2 weeks, a home sleep study to screen for sleep-disordered breathing (SDB) is organized. If participants are eligible for the study, randomization to either auto-titrating continuous positive airway pressure (CPAP) or nasal dilator strip (control group) takes place. Participants follow-up with the study nurse every 2 weeks to verify adherence to therapy and complete study measurements. Post-partum, participants are invited back for a repeat sleep study ~12 weeks after the study is completed and also complete an oral glucose tolerance test as part of routine follow-up with the endocrinologist.

### Participants

Participants are screened for eligibility if they are pregnant women aged ≥18 years referred to the GDM clinic between >20 and <34 weeks gestational age with a diagnosis of GDM. Participants receive a diagnosis of GDM prior to their first study visit based on a positive non-fasting screening 50-g glucose load (24–28 weeks gestation) of >11.1 mmol/L. If this test is abnormal but not in the diabetic range (7.8–11.1 mmol/L), then a fasting, standard, 75-g oral glucose tolerance test (OGTT) is ordered. GDM is defined at our center with either an abnormal 50-g screening test with level ≥11.1 mmol/L or from one of the following from the 75-g OGTT: (1) fasting glucose ≥5.1 mmol/L, (2) 1-h glucose ≥10.0 mmol/L, or (3) 2-hr glucose ≥8.5 mmol/L (49), all in the absence of pre-existing or pregestational diabetes. Screening questions on snoring, witnessed apneas or other symptoms of SDB are not used in the selection process. Participants are not eligible if they had multiple pregnancy, current cigarette smoking or alcohol consumption, chronic renal disease, cardiovascular disease, stroke, active psychiatric disease, active malignancy, HIV infection, Hepatitis C or B, prior treatment for SDB, occupation involving shift work or travel across time zones, or inability to provide informed consent.

Within 1 week of the initial GDM clinic visit, participants are scheduled for a one-night level 2 screening home polysomnogram. A sleep technologist sets up the complete polysomnogram (Titanium unit, Medcare, Natus Inc., Mississauga, ON) in the participant's home in the evening and verifies all signals. Following the sleep recording, a driver picks up the device from the participant's home and returns it to our sleep laboratory. Data from the recorder is downloaded and studies are scored by a Registered Polysomnographic Technologist with review by one of the study sleep physicians (SP, [name]). Standard quality assurance measures for scoring reliability are applied including ensuring a minimum of ~4 h of total sleep time. In addition, oximetry, electroencephalography (EEG), and nasal cannula signals are verified for adequate quality, which is necessary for accurate scoring of respiratory events. Sleep-wake state, arousals and periodic limb movements are scored in accordance with current AASM criteria (50); respiratory events are scored using standard Chicago criteria (51). A diagnosis of SDB establishing eligibility for randomization is made based on the presence of an apnea-hypoponea index (AHI) ≥10 based on Chicago respiratory scoring criteria. Since pregnancy is generally characterized by milder SDB and lesser degrees of oxygen desaturation (21, 52–55), the more sensitive Chicago scoring criteria were chosen for diagnosis of SDB.

Potential participants in whom sleep studies demonstrate severe SDB (AHI ≥30 events/h) with significant sleepiness (ESS ≥15), or significant oxygen desaturation regardless of symptoms (4% oxygen desaturation index ≥30 or sustained hypoxia <80%) are excluded and sent for urgent evaluation at the Sleep Clinic at our institution.

### Randomization

Eligible participants are randomized using web-based randomization with permuted blocks of varying size (Dacima software, Montreal, Quebec).

### Treatment interventions

#### Experimental group

Nightly CPAP treatment until delivery: In the participants randomized to the active intervention arm, auto-titrated CPAP (auto-CPAP) is started within 2 weeks of the initial GDM clinic visit following a positive sleep study for SDB. Active arm participants receive an individualized 1 h session on set-up, mask-fitting and preference, and potential side-effects (e.g., dry mouth, nasal congestion). A variety of nasal masks are initially tried for comfort during set-up, but if mouth-breathing, or intolerance to the nasal mask occurs, an oronasal mask is fitted. Education, troubleshooting of side effects occurs every 2 weeks, and more often as necessary by telephone or in-person visits. Download of the CPAP adherence data (adherence, leaks, pressure settings, efficacy with residual AHI) occurs either by Wi-Fi using available software or by interrogation of the memory chip at specific visits every 2 weeks (Figure 1) (56). All participants assigned to CPAP are encouraged to use the device for the remaining period of pregnancy (~8 weeks) for as many hours during sleep as possible.

#### Control group

Significant uncertainty exists on the optimal control group for CPAP studies. In particular, in pregnant women, a sham CPAP group may likely interfere with sleep quality and may shorten sleep duration. These effects may worsen glucose control and bias the results in favor of the active intervention arm. For these reasons, nightly nasal dilator strips are being tested in this population as a possible control. The strips (Breathe Right®, GlaxoSmithKline, Brentford, UK) mechanically pull the lateral nasal walls outward, causing nasal passage dilatation, thereby easing breathing and reducing snoring, but not SDB, in the general population (57). Since nasal strips have not been evaluated thoroughly in pregnancy, we are assessing for adherence in a way that is analogous to a pill count, by monitoring for leftover strips. Side effects and tolerability is also queried during each clinic visit. Control arm participants also complete a level 2 home polysomnogram 2 weeks after starting the nasal strip to determine if any improvements in respiratory parameters occurred.

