### Outcomes

The primary outcome in this study is to objectively determine the adherence to CPAP among women with GDM and SDB. Acceptable adherence is defined by mean usage ≥4 h/night for at least 70% of nights, the conventional threshold for acceptable CPAP adherence in the general non-pregnant population (40–42, 58). Secondary analyses will examine predictors of CPAP adherence (i.e., demographic and SDB severity variables).As a secondary outcome, the suitability of nasal dilator strips as a possible control intervention for a future large-scale, multi-centered RCT in GDM will be assessed. Patient adherence, changes in indices of SDB as assessed by level 2 polysomnography, and changes in sleep quality and daytime sleepiness (questionnaire-based assessments) will be measured.Recruitment and retention rates will be computed at the end of the trial. This will be important in planning a future large scale RCT.The feasibility of measuring glucose levels using CGM in CPAP vs. control groups is also being assessed. CGM provides in-depth information on glucose levels that cannot be obtained from routine blood glucose measurements. We use the well-validated iPro2® (Medtronic, Northridge, CA) CGM (59, 60), a small, minimally invasive device with a painless, subcutaneous sensor measuring interstitial glucose levels every 5 min. These levels are comparable to venous blood glucose measurements (61–63). A trained technician inserts the CGM device subcutaneously in the arm or abdomen, which takes measurements over 3 days to take into consideration day-to-day variability (64). CGM has been used in pregnant subjects previously and is well-tolerated (65). The CGM is blinded so participants cannot see glucose values and will be not be burdened by alarms or sensor inaccuracy. To ensure accuracy of the measurements, CGM requires calibration against capillary blood glucose measurements that are measured as part of standard of care 4 times/day by the participant (61). Insulin requirements are documented at each visit using self-reported insulin doses in patient logbooks. Participants are asked to maintain their usual diet and exercise patterns during this time. Glucose levels between the treatment and control groups will be compared.

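### The strip arm's before-after AHI change cannot show whether nasal strips alter SDB, because women enter on a single-night AHI of at least 10 that also serves as baseline

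*Protocol article*

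**What the plan says.** All places are in the protocol article.

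- **Baseline and entry test (Participants).** After the first GDM clinic visit, "participants are scheduled for a one-night level 2 screening home polysomnogram". The decision on "eligibility for randomization is made based on the presence of an apnea-hypoponea index (AHI) ≥10", scored by the Chicago criteria, comes from that recording. No other sleep study before treatment is described.
- **Upper exclusions (Participants).** Women with AHI of 30 or more are excluded if they also have marked sleepiness. Severe desaturation excludes regardless of symptoms. There is no general ceiling on AHI.
- **Retest (Control group).** Women in the control arm are to "complete a level 2 home polysomnogram 2 weeks after starting the nasal strip to determine if any improvements in respiratory parameters occurred". The same section says that strips ease breathing and snoring in the general population but do not reduce SDB.
- **Use (Outcomes).** Suitability of strips as a control is a secondary outcome. It draws on adherence, "changes in indices of SDB as assessed by level 2 polysomnography", sleep quality and daytime sleepiness.
- **Other arm and other times.** The CPAP arm supplies residual AHI from the device while on treatment (Experimental group). The repeat sleep study for all women comes after delivery (Postnatal).
- **Analysis (Data analysis).** No method is given for the strip-arm sleep-study change.

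**The concern.** A woman enters partly because her AHI was high on one particular night. Some of that height is night-to-night noise, and it does not recur on an independent second night. So the mean of a selected group is expected to fall on retest without any treatment.

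A concurrent group selected in the same way and restudied untreated would absorb this. Here only strip-arm women have an antenatal repeat level 2 study. Randomization therefore does not protect this particular comparison, which is a one-arm change in the selection variable.

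What is at stake is the choice of control for the multi-center trial that this pilot is meant to prepare. An inert strip could look active and count against itself as a control. Conversely, a rise in SDB as pregnancy advances could hide a real strip effect. Neither error would show in the raw change.

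**Working it through.** The plan states no figure for this comparison, so there is none to reproduce. The check asks what a strip with no effect would show.

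**Inputs from the article**
- Entry at AHI ≥10 on one night; one retest at 2 weeks in the strip arm.
- SDB prevalence of 17-45% in pregnancy (Introduction), used only to anchor the assumed distribution.
- 30 women in the CPAP group (Sample size). Table 1 is headed per group and lists 20, 25 and 30, so 20-30 is assumed for the strip arm.

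**Assumptions not in the article**
- Log AHI in screened women is normal with median m = 5 or 8 and SD σ = 0.8 or 1.0. A median of 12 is a milder case.
- The correlation ρ of log AHI between nights (reliability) is 0.6-0.9.
- The strip has no effect, and there is no trend with gestation.

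**Formulas**
- z = (ln 10 − ln m)/σ
- p = 1 − Φ(z), the share reaching 10
- λ = φ(z)/p
- Expected change in log AHI among women selected = −(1 − ρ)σλ
- Geometric-mean ratio, retest to baseline = exp[−(1 − ρ)σλ]
- Share retesting below 10 = (1/p) ∫ from z to ∞ of φ(x) Φ[(z − ρx)/√(1 − ρ²)] dx

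**Two worked cases**
- m = 5, σ = 1.0, ρ = 0.6: λ = 1.285, ratio = exp(−0.4 × 1.0 × 1.285) = exp(−0.514) = 0.60, a 40% fall.
- m = 8, σ = 0.8, ρ = 0.9: λ = 0.984, ratio = exp(−0.1 × 0.8 × 0.984) = exp(−0.079) = 0.92, an 8% fall.

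**Grid, no upper limit on AHI**

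| m | σ | z | p | λ | Ratio, ρ=0.6 | Ratio, ρ=0.9 | Below 10, ρ=0.6 | Below 10, ρ=0.9 |
|---|---|---|---|---|---|---|---|---|
| 5 | 0.8 | 0.866 | 0.19 | 1.419 | 0.64 | 0.89 | 51% | 25% |
| 5 | 1.0 | 0.693 | 0.24 | 1.285 | 0.60 | 0.88 | 47% | 23% |
| 8 | 0.8 | 0.279 | 0.39 | 0.984 | 0.73 | 0.92 | 36% | 18% |
| 8 | 1.0 | 0.223 | 0.41 | 0.945 | 0.69 | 0.91 | 35% | 17% |
| 12 | 0.8 | −0.228 | 0.59 | 0.659 | 0.81 | 0.95 | 24% | 12% |
| 12 | 1.0 | −0.182 | 0.57 | 0.686 | 0.76 | 0.93 | 25% | 12% |

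For medians 5-8, 19-41% of screened women reach 10, which sits within the cited 17-45%. The ratio runs from 0.60 to 0.92, or to 0.93 if AHI above 60 is left out. That is a fall of roughly 7-40%. For a median of 12 the fall is about 5-24%. With ρ = 1 it is zero, so the artefact comes only from night-to-night noise.

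**Sensitivity to the exclusion of severe cases.** Dropping every woman with AHI ≥30 is stricter than the protocol's rule. For medians 5-8 the geometric-mean ratio is then 0.64-0.94. The arithmetic mean is less regular: without the limit it falls by 0.8-5.3 events/h, and with it the change runs from −3.4 to +0.4.

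**Illustration of the consequence.** The article names no test. If a routine two-sided 5% paired t-test on log AHI were used, simulation for medians 5-8 gives a significant fall with an inert strip in about 14-83% of trials with 20 women and 20-96% with 30. The nominal rate in that direction is 2.5%.

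**The case against.** The strongest reply is that the article commits to no analysis of this change. It says that the indices will be measured and leaves the method open, and an analysis plan that is not shown may handle it. This stands as far as the choice of test goes: no naive paired test can be held against the sponsor. It does not dispose of the point. The article itself fixes the one-night selection, the one-arm retest and the purpose of looking for improvement, and a routine paired test or confidence interval would leave the bias in place.

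A reader might infer more than the text supports:

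- **That an inert strip will certainly look effective.** The expected bias from regression is downward, but the Introduction describes pregnancy changes thought to raise SDB risk, and these could offset it. On the arithmetic mean, the partial exclusion of severe cases could also shrink the fall. In addition, the article speaks of respiratory parameters and SDB indices, not AHI alone; regression is strongest for AHI because women are selected on it.
- **That the AHI change alone decides whether strips are suitable.** It is one of several measures in Outcomes, side effects and tolerability are also recorded, and no rule says that a fall rejects strips.
- **That the size is known.** Reliability and the AHI distribution are assumed throughout. High reliability or a higher median makes the artefact modest.

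The statement that no untreated antenatal comparison exists rests on the text and the caption of Figure 1; the graphic itself was not available.

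**Conclusion.** The concern holds as a limit on interpretation. As designed, the strip arm's raw before-after change cannot show whether strips alter SDB. Regression to the mean pulls AHI down, gestational worsening may push it up, and nothing in the antenatal design separates either from a strip effect.

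The direction of the regression bias follows from the design whenever reliability is below 1. Its size rests on the assumptions listed above and ranges from small to large enough to be mistaken for a treatment effect. It bears on one component of a secondary outcome. CPAP adherence, recruitment, retention and the between-arm glucose comparison do not depend on it. It is worth correcting because choosing a control for the later trial is one of the pilot's declared purposes.

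**What to change.** State in Control group and in Outcomes, and carry into the analysis plan, that:

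1. the strip-arm change in AHI will be reported descriptively with its 95% CI;
2. beside it will stand the change expected with no strip effect, computed from the AHI distribution of all screened women, including those below 10, over a stated reliability range (for example 0.6-0.9);
3. neither a strip effect nor unsuitability as a control will be inferred from the raw before-after change alone.

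A stricter rule, which claims an effect only if the whole interval lies beyond the expected range, is not recommended. With a reliability range of 0.6-0.8, simulation suggests that it would detect a true 30% reduction in only about 13-83% of trials with 30 women.

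**Cost.** A few sentences and a short calculation on screening data already collected, with no added visits. The downsides are that reliability remains assumed, and that the pilot will give no firm answer on whether strips alter AHI, so a truly active strip might not be identified. A firm answer would need a pre-treatment night not used for selection or a concurrent group restudied without strips. The first removes the regression but not the gestational trend; the second addresses both.
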